## 6.3 Study design

### 6.3.1 Overview of the study design

[figure not shown]

### 6.3.2 Trial design

A cross-sectional nutrition baseline survey targeting household with children under the age of two years will be conducted to assess the outcome indicators prior to the intervention in the selected areas in September 2012. Based on the results of the baseline restricted randomization will be conducted to identify intervention and control areas. MALIS will disseminate nutrition education and improved complementary feeding recipes gathered from TIPs in the FAO EU Food Facility project in Cambodia in selected households in the intervention area. After at least 18 months of intervention of nutrition education and complementary feeding counseling which will be conducted by MALIS a cross-sectional impact survey will be conducted to evaluate, whether improved complementary feeding practices and recipes

developed by TIPs have had an impact on the nutritional status of children below two years. The impact survey is scheduled for 2015.

### 6.3.3 TIPs and Intervention

TIPs has already been conducted under the FAO EU Food Facility Project in nine provinces in Cambodia from 2009 to 2011 (see Chapter 2.2.1). The intervention will be a wider dissemination of the improved recipes and behavior change messages developed through TIPs. During the dissemination phase data collection will include monitoring data on the dissemination and roll out of the behavior change messages through MALIS.

## 6.4 Sample size for baseline and impact survey

The appropriate sample size for the cross-sectional baseline survey will be determined largely by three factors (52):

- a) estimated prevalence of the variable of interest,
- b) desired level of confidence, and
- c) acceptable level of error.

Using ENA for Smart sample size calculator (49) and considering a population size of 15000 children under two in the surveyed area, 50% of stunting (key indicator), desired precision of +/- 5% and a design effect of 3 the sample size calculation results in 1124 children. Avillage is the cluster unit.

The cross-sectional impact survey sample size will be based on the formula proposed by Haynes and Moulton for cluster randomized trials Haynes and Moulton (50):

$$n = (z_{\alpha/2} + z_{\beta})^2 \frac{(\sigma_0^2 + \sigma_1^2)}{(\mu_0 - \mu_1)^2}$$

The sample size calculation resulted in 335 children for each treatment arm, considering a power of 80%, confidence level of 95%,  $\sigma_0 = 1.5$  and  $\sigma_1 = 1.2$  and estimated 15% increase of HAZ ( $\mu_0 = -1.96$ ,  $\mu_1 = -1.66$ ).

Nevertheless, to adjust for intra-class correlation (ICC), a design-effect should be included. The design effect (DEFF) is defined as:

---

Values have been estimated from the available literature.

$$DEFF = 1 + ICC (m-1)$$

Considering that  $m=19$  children per cluster (village) will be measured, and an estimated ICC of 0.03 is applied (see annex 10.3), the  $DEFF= 1 + 0.03*18=1.54$ . Multiplying the DEFF-value with the above calculation this results in 516 children below two for each treatment arm. Adding an extra 10% to account for drop-outs or non-responders results in a sample size of 568 children below two years for each treatment arm.

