## 4 Hypothesis

Assuming that behavior change messages on breastfeeding and complementary feeding practices as well as hygiene aspects as generated by the TIPs are widely accepted and out into practice by the mothers with children ages 0-23 months the data assessment will be based on the following hypotheses:

1. The Height for age Z-Score (HAZ) of children below 2 years will increase if TIPs recommendations and recipes are locally available and accepted. At conclusion of the intervention, there will be a difference of 15% of the HAZ between interventions and controls:

$$H0: \mu \text{ HAZ (intervention)} = \mu \text{ HAZ (control)}$$

$$H1: \mu \text{ HAZ (intervention)} > \mu \text{ HAZ (control)}$$

2. Secondly, prevalence of anemia, vitamin A deficiency as well as morbidity rates will be reduced:

a) Anemia (A) among children between 6 and 23 months, defined as hemoglobin level of < 11g/dl, will decrease by 25 %:

$$H0: P(A| \text{intervention}) = P(A| \text{control}),$$

$$H1: P(A| \text{intervention}) < P(A| \text{control})$$

b) Retinol binding protein (RBP) levels will decrease by 15% among children with a C-reactive protein (CRP) level of < 12mg/l:

$$H0: \mu \text{ RBP (intervention)} = \mu \text{ RBP (control)},$$

$$H1: \mu \text{ RBP (intervention)} < \mu \text{ RBP (control)}$$

c) Prevalence of children with presumed acute respiratory infections and fever (ARI) and diarrhea (D) in the last two weeks prior the survey will decrease by 25%:

$$H0: P(ARI| \text{intervention}) = P(ARI| \text{control}),$$

$$H1: P(ARI| \text{intervention}) < P(ARI| \text{control})$$

$$H0: P(D| \text{intervention}) = P(D| \text{control}),$$

$$H1: P(D| \text{intervention}) < P(D| \text{control})$$

d) There will be differences in knowledge of age-appropriate complementary feeding (KCF) of children between caretakers measured using a knowledge score in interventions and controls.

H0:  $\mu$  KCF (intervention) =  $\mu$  KCF (control),

H1:  $\mu$  KCF (intervention) >  $\mu$  KCF (control).

e) TIPs formative research generates nutritionally improved, culturally acceptable and affordable recipes which result in improved feeding practices and food intake which will result in a higher dietary diversity score for the children.

There will be differences in dietary diversity (DD) between interventions and controls:

H0:  $\mu$  DD (intervention) =  $\mu$  DD (control),

H1:  $\mu$  DD (intervention) >  $\mu$  DD (control).

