## 6.5 Randomization procedure

A simple randomization proportional to population per district will be conducted to select 75 survey villages for the baseline. In each village 15 households with children under two will be randomly selected. In case there are less than 15 households with children under two in the selected village, the missing number of households will be randomly selected from the closest neighbouring village. The intervention and control villages are assigned following a restricted randomization based on the results of the baseline survey.

This implies that randomization will take place after adjusting for certain variables that might interfere with variables of interest to the study. Variables of adjustment are:

- district officer
- level of stunting
- total village population
- average land holding size
- wealth status
- access to health posts, nutrition rehabilitation unit, or nutrition counseling by a NGO

The selected clusters will be the objective of randomization. Randomization will be done using the Software package “Experiment” and the operation “randomize”. The “Experiment”-package is a software extension to the statistical software  $R^{\circledast}$ . It serves to design and analyze different types of randomized trials, including cluster randomized trials, block, or matched pair designed trials (60). The baseline and the impact survey will randomly select the study participants in the selected clusters.

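### The sample size assumes, without a reason, a smaller HAZ standard deviation under intervention (1.2) than under control (1.5), and the stated 80% power depends on it

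*Protocol*

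**What the plan says.** Protocol Section 6.4 compares two means with a formula that has a separate variance term for each arm. Its inputs are "considering a power of 80%, confidence level of 95"%, σ0 = 1.5, σ1 = 1.2, μ0 = -1.96 and μ1 = -1.66. Index 0 is evidently control and index 1 intervention, because the second mean is the first after the "estimated 15% increase of HAZ". The result is given as follows: "The sample size calculation resulted in 335 children for each treatment arm". A design effect of 1.54 raises this to 516, and a 10% allowance for non-response to 568. The only support for the inputs is a footnote: "Values have been estimated from the available literature".

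Two other sections bear on the choice of SD. Section 4, item 1, puts the primary hypothesis in terms of means: "At conclusion of the intervention, there will be a difference of 15% of the HAZ between interventions and controls". Its null and alternative hypotheses compare mean HAZ and do not mention spread. Section 6.5 says how the arms are formed: "The intervention and control villages are assigned following a restricted randomization based on the results of the baseline survey". Level of stunting is among the adjustment variables there.

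**The concern.** Restricted randomisation divides one pool of villages into two arms, balancing on stunting among other factors. Without an intervention effect, the arms have the same HAZ distribution in expectation and therefore one SD. A smaller SD in the intervention arm is thus an assumed effect of the intervention, additional to the mean shift that Section 4 hypothesises. The protocol nowhere says that counselling and recipes will narrow the spread of HAZ, and the footnote does not explain why the arms should differ.

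The assumption matters because a lower σ1 reduces the required number of children. If the intervention moves the mean and leaves the spread alone, the stated power holds only if the common SD happens to be low enough.

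**Working it through.** **Inputs.** From Section 6.4: σ0 = 1.5, σ1 = 1.2, two-sided 5% (the formula uses z for α/2), power 80%, design effect 1 + 0.03 × 18 = 1.54, 10% added. The difference is 15% of 1.96 = 0.294; the rounded means give 0.30.

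**Reproducing the plan.** n = (1.96 + 0.8416)² × (σ0² + σ1²) / d².

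- With d = 0.294: 7.849 × (2.25 + 1.44) / 0.08644 = 335.1, which matches 335.
- With d = 0.30 the result is 322, so the plan used 0.294.
- 335 × 1.54 = 515.9, stated as 516; 516 × 1.1 = 567.6, stated as 568.

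The unequal SDs are therefore what produced the published figures. The assumed variance reduction is 1 - 1.44/2.25 = 36%.

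**One SD in both arms.** The 516 analysed children per arm are worth 516/1.54 = 335 independent ones.

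- Power = Φ(0.294 / (s × √(2/335)) - 1.96), with √(2/335) = 0.07727.
- Difference detectable with 80% power = 2.8016 × s × 0.07727 = 0.2165 × s.
- Required n per arm before clustering = 7.849 × 2s² / 0.08644.

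| Common SD | Where it comes from | Power at 335 effective | Detectable difference | n per arm for 80%, before clustering |
|---|---|---|---|---|
| 1.5 | plan's control value | 71.8% | 0.325 | 409 |
| 1.36 | plan's average variance, √((2.25 + 1.44)/2) | 79.9% | 0.294 | 336 |
| 1.27 | normal fit to Table 1, under two years | 85.0% | 0.275 | 293 |
| 1.2 | plan's intervention value | 88.7% | 0.260 | 262 |

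At SD 1.5, the 409 become 630 after the design effect and 693 with 10% added, against the stated 516 and 568. Power at SD 1.5 is 73.5% if the difference is 0.30. If all 568 per arm respond (568/1.54 = 369 effective), it is 75.9% at 0.294.

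**The Table 1 value.** Weighting the five under-two rows of Table 1 by their n (total 1,541) gives 28.5% below -2 and 8.8% below -3. The matching normal quantiles are -0.569 and -1.354, so SD = 1/(1.354 - 0.569) = 1.27. The same fit puts the mean at -2 + 0.569 × 1.27 = -1.28, well above the plan's control mean of -1.96. These national data are therefore an indication only and do not settle the SD in the two study provinces.

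**The case against.** The formula has separate variance terms, so unequal SDs are allowed and the plan's arithmetic is right. That stands: this is an unsupported input, not a calculation error.

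A reader might infer that power is really 72% and not 80%. The documents do not support that. The figure comes from taking the larger of the two SDs for both arms, and the protocol does not say that 1.5 is better founded than 1.2. One SD with the plan's own average variance leaves power at 80%, and the only other evidence on spread in the document, Table 1, points to a lower SD and higher power. This also stands.

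A reader might also note that two normal curves with these means and SDs cross one SD above their means (-1.96 + 1.5z = -1.66 + 1.2z at z = 1), and infer that the tallest 16% of children would be made shorter. That does not follow. Two marginal distributions do not identify effects on individual children, and planning SDs are not claims about the tails.

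An intervention that helps the most stunted children most could reduce variance, and a hypothesis about means does not exclude this. That is possible, but the protocol does not argue it and gives no figure for it. Finally, the alternative in Section 4 is directional, and a one-sided 5% test at SD 1.5 would have 81.4% power; but Section 6.4 sizes the trial with the two-sided quantile, so its 80% is a two-sided figure.

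**Conclusion.** The point holds as one about an unexplained planning assumption. The 335, 516 and 568 per arm and the 80% power rest on a 36% lower HAZ variance under intervention, which neither the randomised design nor the stated hypothesis supplies. With a common SD, power ranges from 72% to 89% as the SD goes from 1.5 to 1.2, with break-even near 1.36.

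Whether the trial is underpowered cannot be decided from the protocol, and it should not be described as underpowered. These figures take the difference of 0.294, the ICC of 0.03, 19 children per village and the two-sided 5% level as planned; the 1.27 also assumes normality and national data.

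**What to change.** In Section 6.4, replace the two SDs with one common SD and state power and detectable difference over 1.2 to 1.5, as in the table above. If a smaller SD under intervention is to be kept, give the reason and the source.

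After the baseline survey, and before the size of the impact survey is fixed, insert the observed baseline HAZ SD for both arms and restate the power and the detectable difference. About 1,124 children suffice: even if the plan's baseline design effect of 3 applied to the SD, 1,124/3 = 375 effective children give a relative standard error near 1/√(2 × 375) = 3.7% under normality, enough to tell 1.2 from 1.5.

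The cost is a recalculation with data already being collected. The downside is a less favourable stated power if the SD proves near 1.5. The sponsor would then have to accept a detectable difference of about 0.325 or plan for about 630 analysed (693 sampled) per arm, but would know this while the survey size is still open.

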## 6.5 Randomization procedure

A simple randomization proportional to population per district will be conducted to select 75 survey villages for the baseline. In each village 15 households with children under two will be randomly selected. In case there are less than 15 households with children under two in the selected village, the missing number of households will be randomly selected from the closest neighbouring village. The intervention and control villages are assigned following a restricted randomization based on the results of the baseline survey.

This implies that randomization will take place after adjusting for certain variables that might interfere with variables of interest to the study. Variables of adjustment are:

- district officer
- level of stunting
- total village population
- average land holding size
- wealth status
- access to health posts, nutrition rehabilitation unit, or nutrition counseling by a NGO

The selected clusters will be the objective of randomization. Randomization will be done using the Software package “Experiment” and the operation “randomize”. The “Experiment”-package is a software extension to the statistical software  $R^{\circledast}$ . It serves to design and analyze different types of randomized trials, including cluster randomized trials, block, or matched pair designed trials (60). The baseline and the impact survey will randomly select the study participants in the selected clusters.

## **6.6 Statistical methods and analysis**

Data assessment and data analysis will follow the adopted UNICEF framework of underlying causes of malnutrition and mortality (see Chapter 3.1). Nutritional status will be interpreted as a result of household food security, i.e. access to food and food availability, adequate social and care environment, i.e. direct caring behaviors, women's role, status and rights, social organizations and networks, and functioning public health system, i.e. health environment and access to health.

The cross sectional surveys will be used to gather information of the above mentioned parameters before and after the intervention. The data will be entered into the SPSS editor (IBM SPSS Statistics version 20) and checked for inconsistencies by two individuals independently. Flagged values will be checked based on the filled questionnaires and if applicable the study participants will be approached to verify the result.

Statistical analysis will be performed using the statistical packages of IBM SPSS statistics (version 20). At first the variables will be tested for normal distribution, followed by a descriptive analysis of prevalence of malnutrition, anemia, vit-A deficiency, respiratory infections and fever (ARI), diarrhea, morbidity rates, dietary diversity, and knowledge of age appropriate feeding. The latter involves a development of a score to describe the knowledge about age appropriate feeding. Further, regression analysis will be applied looking for causalities of malnutrition in the studied area.

Focus group discussions will be based on a general interview guide approach. The interview guide will include subjects of implementation, acceptance and obstacles of TIPs. They will be analyzed by applying the content analysis according to Mayring (51) and facilitated by the use of MAXQDA©-software (53).

## **6.7 Ethical considerations**

Ethical approval will be applied for at the Institutional Review Board (IRB) of the Faculty of Medicine of the Justus Liebig University Giessen and local National Ethics Committee for Health Research of the Ministry of Health, Cambodia, prior to commencement of the study.

### **6.7.1 Recruitment, risks and benefits**

List of possible eligible participants will be obtained from official population's list.

There is no risk to the participants involved in the study.

**Benefits to Participants:** This study has an indirect benefit to the participants. The study does provide an opportunity for the participants to gain information about their and their children's current nutritional and health status. Participants will receive a "Participants-Card" including their and their children's health data available directly in the field (anthropometric data, age and hemoglobin level). The card will provide information whether the anthropometric measurements or the measured hemoglobin level indicate poor nutritional status. In case of abnormal results participants will be sent for nutrition counseling/ or treatment according to the guidelines of Cambodia for treatment of anemia and malnutrition.

### **6.7.2 Informed consent**

Prior to the surveys, general consent of the EU FAO project communities to participate in this trial will be obtained. Written consent will be obtained by the individual household to be interviewed at the day of data assessment.

The Investigators will be responsible for ensuring informed consent is obtained before any protocol specific procedures are carried out. The decision of a participant to participate in the research study is voluntary and will be based on a clear understanding of what is involved. Participants will receive adequate oral and written information about the nature and purpose of the study, participation/termination conditions, and risks and benefits – appropriate Participant Information and Informed Consent Forms are provided in the Annex. The oral explanation to the participants will be performed by designated people (enumerators), and must cover all the elements specified in the Participant Information Sheet and Informed Consent Form.

The participants will be given every opportunity to clarify any points they do not understand and, if necessary, ask for more information. The participant will be given sufficient time to consider the information provided.

The enumerator and the participant have to sign and date the Informed Consent Form to confirm that consent has been obtained. The participant will be provided with a copy of this document.

## **6.8 Data collection**

The data collection in the cross sectional surveys will be based on an adaptation of the SMART methodology (49). The SMART methodology includes a questionnaire designed to assess mortality, nutritional status and food security in crisis situations. The final questionnaire will consist of standardized modules extracted from the questions designed by the SMART initiative, FAO, WHO, GIZ, and the Manoff Group (1, 6, 49, 54,55-59). Thus, mothers/caretakers with children below two years will be interviewed about their socio-economic situation, food security, mothers' and children's food intake, care, time availability, access to health, water and sanitation, motor milestones, and access to FAO food security activities by trained enumerators. Anthropometric measurements will be taken from mothers, their children below two years of age, and, if possible from fathers, by a nutritionist especially trained in anthropometric measurements. Capillary blood samples will be taken from the surveyed mothers (Hb only) and children below two years to assess the micronutrient status (retinol binding protein (RBP), transferrin receptor (TfR), hemoglobin as well as the morbidity status (C-reactive protein (CRP), acyl glycoprotein (AGP) by medical trained research staff.

### **6.8.1 Interview**

After written consent (see consent form in annex) the caretaker/mother of the child will be interviewed face-to-face by trained enumerators. Depending on the given infrastructure in the villages, participants are either invited in advance to come to a central meeting point, e.g. community center or primary school, to do the interview, or enumerators are coming to the homestead of the participants. If the interviews are conducted centrally in a public place, privacy will be assured by keeping an adequate distance between the interviewed participants that only the enumerators will hear the answers. In case village lists are not available, and systematic sampling is not possible, the EPI method will be used (49). Participants will then be invited on the day of selection to come to central meeting point at a certain time to avoid any inconvenience by waiting.

### **6.8.2 Anthropometric measurements**

A central weighing and measuring station will be installed in every village. After the interview, mothers/caretakers (if possible the father as well) and their children will be

send to the weighing and measuring station. Weight and height of children and adults will be measured according to an anthropometric protocol based on the WHO report “Physical status: the use and interpretation of anthropometry” (1995) (60).

Weight of children will be determined with the child wearing no clothing. Adults’ weights will be taken while wearing light indoor clothing and no shoes. Heights and weights will be assessed to the nearest 0.5 cm and 0.1 kg, respectively. To determine the nutritional status of pregnant women, mid-upper arm circumference (MUAC) will be measured. All measures will be taken twice and the mean value is used for analysis (see ISAK manual (61)).

Anthropometric measurements will be taken with standardized equipment from Seca (SecaGmbH & Co KG, Hamburg, Germany). Weight will be measured using standardized digital flatscales (Seca 874, capacity: 200 kg) with mother/child function. Infants and small children are weighed while being held by the mother. The weight of the mother is assessed separately. Then the Mother-Child function ascertains the tare of the weight. Recumbent length will be taken from children with measuring boards (Seca 417, measurement range: 10–100 cm).

The height of adults will be measured with a stadiometer (Seca 213, measuring range: 20 – 205 cm). A non-stretchable measuring tape will be used to take MUAC (Unicef). After the weight and length assessment the children will be tested for edema. Edema will be diagnosed by applying moderate finger pressure on the tops of the child’s feet. If there is edema, an impression will clearly remain for at least a few seconds (on both feet). Edema will be recorded as absent, mild (both feet/ankles), moderate (both feet/ankles plus lower legs, hands or lower arms) and severe (generalized edema including both feet, legs, hands, arms, and face) (49).

Two pairs of trained research staff, each consisting of a measurer and an assistant, will take all measurements. Privacy of the participants while taking their measurements will be assured.

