## **1 Abstract**

Undernutrition remains one of the biggest challenges in developing countries. Children aged 0-23 months are the most vulnerable group with a peak incidence of mortality and morbidity. The Cambodian Demographic and Health Survey 2010 estimated a national stunting prevalence of 40%. Results show that stunting increases after six months of age when most children receive complementary feeding. The promotion of a nutrient-dense diet based on locally available foods is essential to improve the nutritional status of young children. In order to optimize infants and young children's diets, the FAO project "Improving food security and Market Linkages for Smallholders in Otdar Meanchey and Preah Vihear Provinces (MALIS)" will implement a food security project with a nutrition education component.

The objective of the research is to evaluate the effectiveness of the behavior change messages which will be delivered through a community based intervention involving community based organizations. The research design encompasses both qualitative and quantitative methods, including two cross-sectional surveys, focus group discussions and key informant interviews. The first cross-sectional survey will take place prior to the intervention to assess the baseline nutrition security situation of families with children below two years in the MALIS project region. The behavior change communication strategies will be implemented in the prior selected intervention areas by the MALIS project. The second cross-sectional survey will be conducted after at least 18 months of intervention evaluating the impact of the intervention by a research team.

The primary outcome parameter to be measured will be mean Height for Age z-Scores (HAZ). Secondary outcome parameters will be vitamin A deficiency, iron deficiency and behavior change. Methods for data collection will include anthropometric measurements, questionnaires, collection of blood plasma by finger prick and focus group discussions. Statistical analysis will compare primarily the difference of the mean height-for-age z-score of children in intervention and control areas.

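### Child length, on which the primary outcome rests, is read only to 0.5 cm (about 0.2 HAZ), and nothing keeps the measurers unaware of village allocation

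*Protocol*

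**What the plan says.** Section 1 (Abstract) fixes the endpoint: "The primary outcome parameter to be measured will be mean Height for Age z-Scores (HAZ"). Section 6.8.2 opens by putting everyone under one procedure, "Weight and height of children and adults will be measured according to an anthropometric protocol", and then sets the reading unit: "Heights and weights will be assessed to the nearest 0.5 cm and 0.1 kg, respectively". The method for children follows, "Recumbent length will be taken from children with measuring boards (Seca 417, measurement range: 10–100 cm"), without a unit of its own, so 0.5 cm applies to infants as it does to adults. On replication it says "All measures will be taken twice and the mean value is used for analysis", and on staffing "Two pairs of trained research staff, each consisting of a measurer and an assistant, will take all measurements".

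The measuring station stands in each village, and the village is the unit that is allocated (section 6.5). Section 6.9.4 provides for training, supervision visits and retraining. Neither there nor elsewhere does the protocol say whether the measurers know, or should not know, which villages received the intervention.

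**The concern.** Half a centimetre is a reasonable unit for adult stature but a coarse one for a child under two, where it is a substantial fraction of the reference SD. When a moving infant's length falls between two marks, the measurer decides which mark to record. If the measurer knows the village's arm, that decision can lean one way without any conscious intent, and the size of the possible lean is set by the size of the step. A lean that differs by arm goes directly into the primary comparison, and no later analysis can remove it. Reading unit and assessor masking are matters of conduct. They have to be settled before data are collected.

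**Working it through.** **Inputs.** From section 6.8.2: reading unit 0.5 cm. From section 6.4: HAZ SDs 1.5 and 1.2, means -1.96 and -1.66 (difference 0.30; 15% of 1.96 is 0.294), power 80%, confidence 95%, design effect 1.54, 516 children per arm. Assumed, because the documents give no figure: length-for-age SD of 2.0 to 3.05 cm over 0-23 months, with 2.5 cm as a middle value.

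**1. The plan's own figure.** n = (1.960 + 0.842)² × (1.5² + 1.2²) / δ² = 7.849 × 3.69 / δ². With δ = 0.294 this is 335, as printed. Then 335 × 1.54 = 516 and 516 × 1.1 = 568, also as printed. (The rounded δ of 0.30 would give 322; this does not affect the present point.)

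**2. Size of one step.** Step in HAZ = 0.5 / SD.

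| Length SD (cm) | 0.5 cm step | Half-step | Half-step / 0.30 | Half-step at 0.1 cm |
|---|---|---|---|---|
| 2.0 | 0.25 | 0.125 | 42% | 0.025 |
| 2.5 | 0.20 | 0.10 | 33% | 0.02 |
| 3.05 | 0.16 | 0.08 | 27% | 0.016 |

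**3. The rule as written (nearest mark).** Rounding variance is step²/12. At SD 2.5 cm this is 0.20²/12 = 0.0033, against an average HAZ variance of 3.69/2 = 1.845, an increase of 0.18% for a single reading. Averaging two readings roughly halves it, hence about 0.1 to 0.2%. In simulation the mean difference between arms did not move. Simulating the age mix of Table 1 (assumed HAZ mean -1.5, SD 1.35), stunting status changes for about 0.9% of children with duplicates averaged and 1.4% with a single reading. At 0.1 cm the figures are 0.2 to 0.3%.

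**4. Rounding that differs by arm.** The standard error of the difference is √(1.54 × 3.69 / 516) = 0.105. Suppose one arm is consistently read half a step away from the other, 0.10 HAZ, with no true effect. The standardised shift is 0.10 / 0.105 = 0.95, and two-sided rejection is Φ(-1.96 + 0.95) + Φ(-1.96 - 0.95), about 16% instead of 5%. A shift of 0.05 gives 8%. The same habit on a 0.1 cm scale shifts HAZ by 0.02; 0.02 / 0.105 = 0.19, and rejection stays near 5%.

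**5. Do the duplicate readings still work?** For rounding to the nearest mark, two readings d cm apart (d below 0.5) fall on different marks with probability d/0.5, so readings 0.2 cm apart differ 40% of the time. With an assumed reading error of 0.3 cm, about 58% of pairs still differ. The mean of two readings also falls on a 0.25 cm grid.

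**The case against.** The strongest reply is that the written rule is harmless. The protocol says nearest, and step 3 shows that nearest-mark rounding costs nothing worth counting. A shift of 0.10 HAZ requires a habit the protocol does not prescribe, such as always reading the last completed mark, applied throughout one arm and not in the other. All of that stands, and so the 16% is a near-worst case and not a forecast.

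Two further parts of the reply also stand:

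- **A shared habit cancels.** The primary comparison is between arms, so a reading habit confined to one survey moves both arms of that survey alike. With two pairs taking all measurements, one pair's habit matters only if the pairs are unevenly spread over the arms, and nothing suggests that they are.
- **The interview is not shown to be a leak to the measurers.** It comes before measurement and covers "access to health, water and sanitation, motor milestones, and access to FAO food security activities by trained enumerators", but enumerators conduct it, and section 6.8.1 keeps centrally held interviews out of others' hearing. FAO access is also listed last, after food intake and motor milestones, although a list does not fix the questionnaire order.

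The reply does not dispose of two facts. The unit is explicit and avoidably coarse for this endpoint, and the measurers work inside allocated villages with no instruction about allocation. Training and supervision under section 6.9.4 address consistency of technique; they do not address knowledge of the arm.

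**Conclusion.** The point holds as a cheap improvement, not as a flaw that invalidates the design. One reading step is worth more than half of the target difference (0.16 / 0.30 = 54% to 0.25 / 0.30 = 83%), and a half-step is 27 to 42% of it. The protocol leaves open the one condition under which that matters, rounding that depends on arm. The HAZ conversions rest on assumed length SDs of 2.0 to 3.05 cm. The masking part rests on the protocol's silence; it nowhere states that measurers know the allocation.

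A reader might infer more, and the documents do not support it:

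- That 0.5 cm reading by itself biases the result or costs power. Step 3 shows that it does not.
- That the duplicates are pointless because they nearly always agree. Step 5 shows that they do not.
- That the restriction of the randomisation on "level of stunting" is spoiled. That variable is measured at baseline, before allocation exists. At 1.4%, 15 children give 15 × 0.014 = 0.2 misclassified children per village. The sampling error of a village proportion at the 50% stunting used in section 6.4 is √(0.5 × 0.5 / 15), about 13 percentage points.

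**What to change.** In section 6.8.2, give child recumbent length its own unit: nearest 0.1 cm, with one rounding rule stated for all teams and both surveys. The 0.5 cm unit can stay for adults if wanted. Add that the measuring pairs at the impact survey are not told the allocation of the village they are working in.

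The cost is a changed recording unit and one instruction to field supervisors, with no extra staff or procedure. There are two limits. Masking will be imperfect where project activities are visible in the village, which is a further reason to want the finer unit. The finer unit also assumes that the measuring board has millimetre marks, which the protocol does not state and which should be checked.
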